### Outcome measures

2.3

In our experiment, patient information scale, the life quality scale (The Left Ventricular Dysfunction Scale) and Self-Care of HF Index are utilized for the assessment.

### Statistical analysis

2.4

All the analyses are implemented with SPSS for Windows Version 20.0. And the data are represented by using proper features, for example, percentage, standard deviation as well as mean. Independent samples *t*-test are utilized for comparison between groups. In order to compare the categorical variables between groups, we utilize the Chi-square test. For the significance level, the value of *P* needed to be less than .05.

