### Randomization

2.1

This study includes 90 HF patients. A random number is assigned to all the patients through utilizing via using a random number table, and the allocation result is hidden in a random envelope. Patients are divided randomly into the study group and control group, each group is assigned 45 people. The patients with the following criteria will be excluded: patients who have received the by-pass surgery in the last 6 months; cancer patients are given radiotherapy or chemotherapy; patients with severe renal failure requiring dialysis; patients with chronic obstructive pulmonary disease who need ventilation; and patients with hearing or visual impairment.

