### Nursing Interventions

2.2

In control group, patients are given the standard nursing in the HF outpatient clinic. The doctor carries on the physical examination to the patient, then prescribes the medicine to patient, ultimately, arranges the appointments of outpatient follow-up. The questions of patients are answered by nurse-researcher.

In intervention group, the patients are given the education manual on the basis of the theory of self-care for HF. Moreover, they are also offered a set of magnetic induction instructions that they should pay attention to in their daily life. The patients are asked to attach magnets to their refrigerators so they could easily follow up on their daily visits and be alerted. After baseline data are taken from patients in intervention group, the patients are followed up by nurse researchers on the phone every 2 weeks for the period of 6 months. Nurse researchers carry out the physical examination for the patients, and provide the personal education and then tell the patients how to carry out some relevant daily monitoring. On the basis of the personal daily lifestyle, the prescribed medications can be adjusted by educational intervention. At the clinic, the patients need to bring the training materials with them. Their symptoms, for instance, the blood pressure, edema, taking additional diuretics as well as the levels of their exercise at home are examined. Through the provision of education manuals and personal education, we strive to improve the knowledge and awareness of the patients. By using the educational manuals designed via nurse researchers, magnet supports the telephone follow-up and educational materials to ensure monitoring of individual symptoms, adherence to treatment, and the identification of symptoms, in an attempt to develop the maintenance of self-care. Outpatient consultation and follow-up also contributes to the management of self-care.

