## Results

3

Impact of experimental programs on outcomes will be illustrated in the Table 1.

**Table 1 T1:** Comparison of clinical outcomes between groups.

Variables	Study group (N = 45)	Control group (N = 45)	*P* value
Self-care maintenance			
Baseline to 2nd mo			
3rd to 4th mo			
5th to 6th mo			
Left Ventricular dysfunction scale			
2nd mo			
4th mo			
6th mo			
Total hospitalization cost			
Average daily hospitalization cost			
Rate of rehospitalization			
Complications			

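### The only stated test for the scale scores, an unadjusted t-test, makes no stated use of the baseline score and so gives up precision that baseline adjustment would recover

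*Protocol article*

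**What the plan says.** The outcome section (2.3) states that "the life quality scale (The Left Ventricular Dysfunction Scale) and Self-Care of HF Index are utilized for the assessment". Section 2.1 gives the size: "This study includes 90 HF patients", and "each group is assigned 45 people".

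Section 2.4 says of the independent-samples t-test: "test are utilized for comparison between groups". For the rest it says "In order to compare the categorical variables between groups, we utilize the Chi-square test" and that the P value "needed to be less than .05". It names no covariate, change score, ANCOVA or repeated-measures model.

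Table 1 in section 3 lists the "Left Ventricular dysfunction scale" in separate rows for months 2, 4 and 6, beside a single P value column and with no baseline row. Self-care maintenance has three rows by period, the first running from baseline to month 2. The table does not say whether these rows are period scores or changes.

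Baseline measurement appears in section 2.2, in the paragraph on the intervention arm: "After baseline data are taken from patients in intervention group", telephone follow-up starts. The article does not list which scales are scored at that point, and it describes no use of the scores in the analysis.

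**The concern.** Life quality and self-care are the two benefits that the article hypothesises, so the analysis of these scales is the core of the trial. A patient's score on such a scale usually predicts the later score on the same scale. A t-test on the follow-up score alone treats that predictable variation as noise. With 45 patients per arm this can matter: the test needs a fairly large effect for good power, and a chance difference between the arms at baseline carries over, in part, into the follow-up difference that the reader sees.

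This is more than a detail left to an unseen analysis plan. The article fixes a method, and a better one is available at almost no cost. At stake are precision and the credibility of the estimate actually observed, not the validity of the test.

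**Working it through.** **Inputs from the article.** 45 per arm (section 2.1); unadjusted independent-samples t-test and significance level 0.05 (section 2.4). The level is taken as two-sided, since the article does not say.

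**Assumptions.** The article gives no SD, target effect, power or correlation, so there is no stated figure to reproduce. I take an effect d = 0.5 SD as an illustration and a baseline to follow-up correlation r of 0.3, 0.5 and 0.7 as the range.

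**Step 1: unadjusted t-test.** Noncentrality = d × √(n/2) = 0.5 × √(45/2) = 2.372, with 88 degrees of freedom. Power is 65%. The difference detectable with 80% power is 0.597 SD.

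**Step 2: baseline-adjusted analysis.** ANCOVA multiplies the residual variance by 1 − r². Estimating the slope costs one degree of freedom (87 remain) and a variance factor of 1 + 1/(2n − 4) = 1 + 1/86 = 1.012. Noncentrality = 2.372 / √[(1 − r²) × 1.012]. The equivalent sample size for a plain t-test is 45/(1 − r²), and the detectable difference is 0.597 × √(1 − r²); these last two leave out the 1.2% factor.

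| r | Cut in residual variance (r²) | Noncentrality | Power at 0.5 SD | Detectable difference, 80% power | Equivalent n per arm |
|---|---|---|---|---|---|
| none (t-test) | 0% | 2.37 | 65% | 0.60 SD | 45 |
| 0.3 | 9% | 2.47 | 69% | 0.57 SD | 49 |
| 0.5 | 25% | 2.72 | 77% | 0.52 SD | 60 |
| 0.7 | 49% | 3.30 | 90% | 0.43 SD | 88 |

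A normal approximation gives 66% unadjusted and 70%, 78% and 91% adjusted, about one percentage point higher throughout.

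**Step 3: chance baseline imbalance.** The standard error of the standardised baseline difference is √(2/45) = 0.211 SD, so its 95% range is ±1.96 × 0.211 = ±0.41 SD. The probability of a difference above 0.3 SD in either direction is 2 × [1 − Φ(0.3/0.211)] = 15%. An imbalance b shifts the expected unadjusted follow-up difference by r × b. For b = 0.3 SD this is 0.09, 0.15 or 0.21 SD at r = 0.3, 0.5 or 0.7.

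**Step 4: is the test still valid?** Given an imbalance of k standard errors, the unadjusted test statistic under no effect has mean r × k and variance 1 − r². At k = 1.96 the conditional type I error is about 8%, 13% or 20% for the three correlations. At k = 1 it is about 5.0%, 4.8% or 3.9%. Over all randomisations the rate is the nominal 5%. Steps 2 and 3 therefore describe the same variance from two sides, and their effects should not be added.

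**Step 5: would change scores do as well?** Their variance is 2(1 − r) times that of the follow-up score. With the same t-test, power at 0.5 SD is about 51% at r = 0.3, 65% at r = 0.5 and 86% at r = 0.7: worse than the plain t-test, equal to it, and better than it, but below ANCOVA each time.

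**The case against.** The strongest reply is that nothing here is an error. In a randomised 1:1 comparison the t-test is unbiased and keeps its type I error, and its standard error already allows, on average, for chance imbalance. That stands. A reader might infer that the planned comparison is biased. Step 4 shows that this is true only conditional on an imbalance that has been observed.

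The size is also open. The gain rests on a correlation that the article does not give; at 0.3 it is only about four percentage points of power. That stands too, and is why the range is shown.

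Three further inferences are tempting but not supported:

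- *Controls have no baseline scores, or baseline is taken after allocation.* Section 2.2 mentions baseline only while describing the intervention arm, and says only that the telephone calls come after it. It gives no timing relative to opening the envelope and says nothing either way about controls. Table 1 is an outcomes table, so the lack of a baseline row in it proves little.
- *Baseline is ignored in every row.* The first self-care row may be a change from baseline. The later self-care rows and all life-quality rows show no such use, so the point is firm for life quality and only apparent for self-care. That there is one test per row is itself inferred from the table layout and the single named test.
- *Patients with missed visits will be lost from the analysis.* Missing-data handling is commonly left to the analysis plan, which is not shown, so this forms no part of the point.

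The reply that the whole matter belongs to the analysis plan does not succeed, because section 2.4 already states the method.

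**Conclusion.** The point holds as a loss of efficiency. The stated t-test is valid, but for the life-quality scale, and apparently for self-care maintenance, it is less precise than a baseline-adjusted comparison and leaves chance baseline imbalance in the observed estimate. In terms of sample size, adjustment is worth between about 4 and 43 extra patients per arm across correlations of 0.3 to 0.7.

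That there is a gain is secure for any correlation of practical size. How large it is depends on the assumed correlation and on the illustrative effect of 0.5 SD. The change is worth making, but results from the t-test as planned would not be invalid.

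**What to change.** Confirm, and state in section 2.2 or 2.3, that both scales are scored at baseline in all 90 patients before allocation is revealed. In section 2.4, replace the unadjusted t-tests on the scale scores with ANCOVA at each time point, with the baseline score of the same scale as covariate, and report the adjusted group difference with its 95% CI. State in Table 1 whether the self-care rows are scores or changes, so that the covariate is well defined.

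A repeated-measures mixed model with baseline as covariate is an acceptable alternative. The choice between the two, the covariance structure and which time point is the main contrast are for the sponsor to decide; this point does not depend on them. Both methods run in SPSS, the stated software.

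The cost is slightly more analysis work, and a baseline questionnaire in controls if it is not already planned.

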## Results

3

Impact of experimental programs on outcomes will be illustrated in the Table 1.

**Table 1 T1:** Comparison of clinical outcomes between groups.

Variables	Study group (N = 45)	Control group (N = 45)	*P* value
Self-care maintenance			
Baseline to 2nd mo			
3rd to 4th mo			
5th to 6th mo			
Left Ventricular dysfunction scale			
2nd mo			
4th mo			
6th mo			
Total hospitalization cost			
Average daily hospitalization cost			
Rate of rehospitalization			
Complications			

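### Separate t-tests on scores repeated to month 6 discard the earlier scores of patients lost later; one repeated-measures mixed model would protect the comparison better at almost no cost

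*Protocol article*

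**What the plan says.** - **Numbers assigned.** Section 2.1 (Randomization) states "This study includes 90 HF patients" and "each group is assigned 45 people". Table 1 in section 3 (Results) carries the same number over each arm: "Variables Study group (N = 45) Control group (N = 45").
- **Repeated scores.** Table 1 lists the Left Ventricular Dysfunction Scale at months 2, 4 and 6. It lists self-care maintenance over three intervals: baseline to month 2, months 3 to 4, and months 5 to 6. The table has one column for P values.
- **Test.** Section 2.4 (Statistical analysis) says "Independent samples *t*-test are utilized for comparison between groups", with the chi-square test for categorical variables. For significance, "the value of *P* needed to be less than .05". No method that uses several time points together is named.
- **Contact.** Under section 2.2 (Nursing Interventions), in the intervention arm "the patients are followed up by nurse researchers on the phone every 2 weeks for the period of 6 months". Control patients receive standard clinic nursing and outpatient follow-up appointments; no scheduled calls are described for them.
- **Loss.** The article gives no expected loss to follow-up.

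**The concern.** A t-test on one row of Table 1 sees only the scores in that row. What a lost patient reported earlier is not used, although with scores correlated over time it says a good deal about the missing value.

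The month-6 difference stays unbiased if loss is unrelated to how patients are doing, or if it works in the same way in both arms. Neither can be taken for granted here. The Discussion describes heart failure as a condition with early death and frequent rehospitalisation, so some missing scores may be related to health. Regular calls in one arm only make different retention plausible. If sicker patients drop out more from one arm, those who remain make that arm look better than it is. Life quality and self-care, the two outcomes in the article's hypothesis, are the ones exposed.

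**Working it through.** **Agreement of the stated numbers.** 90 / 2 = 45, so section 2.1 and the Table 1 heading agree. The figure of 90 cannot be derived further, because the article states no effect size, SD, power or loss.

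**Scale of the trial.** The difference detectable with 80% power at two-sided 0.05 (sidedness assumed) is (1.960 + 0.842) × √(2/n) in SD units.
- n = 45 per arm: 2.802 × √(2/45) = 0.59 SD.
- 20% loss in each arm, n = 36: 2.802 × √(2/36) = 0.66 SD.

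A bias of 0.1 SD is therefore about one sixth of what the trial can detect (0.1 / 0.59 = 0.17).

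**Simulation with repeated visits.** From the article: 45 per arm, scores at months 2, 4 and 6, t-test at 0.05. Assumed: a month-0 score, SD 1, higher is better, correlation 0.6 between visits, and dropout that depends on the last observed score (logit slope 0.7 to 1.0 per SD, worse patients lost more often). The true benefit is 0.5 SD.

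| Loss by month 6, study v control | Month-6 t-test estimate |
|---|---|
| none | 0.50 SD (power 65%) |
| 10% v 25-30% | about 0.39-0.44 SD (power about 37-47%) |
| 25% v 10% | about 0.56-0.58 SD |
| 20% v 20% | 0.50 SD, no bias |

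In the second row about 40 v 32-34 patients remain (45 × 0.90 = 40.5; 45 × 0.75 = 33.8; 45 × 0.70 = 31.5). The bias is 0.50 − 0.44 = 0.06 to 0.50 − 0.39 = 0.11 SD. The fall in power comes partly from this bias and partly from the smaller numbers. With the same unequal loss and no true effect, the false-positive rate is about 5.7-7.6%. Repeat runs differ by about 0.01 SD.

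**Simulation with a single score.** No true effect, 20,000 trials, a fixed number lost per arm, chance of loss proportional to exp(−b × score).

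| Loss, study v control | Patients left | b = 0: bias | b = 0.5 to 1: bias against the study arm | b = 0.5 to 1: false positives |
|---|---|---|---|---|
| 5% v 15% | 43 v 38 | 0.00 | 0.06-0.11 SD | 5.9-8.5% |
| 5% v 20% | 43 v 36 | 0.00 | 0.09-0.15 SD | 7.0-11.5% |
| 10% v 30% | 41 v 31 | 0.00 | 0.13-0.22 SD | 8.9-17.3% |

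The b = 0 column shows that unequal loss alone does not bias the test, even at 10% v 30%. Bias needs unequal loss and a link to the score together.

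**The alternative.** In the repeated-visit simulation, a likelihood analysis using all visits and the baseline score recovered the true effect to within about 0.01 SD. Without the baseline score about a third of the bias remained, that is about 0.06 / 3 = 0.02 to 0.11 / 3 = 0.04 SD.

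**The case against.** **The heading is not wrong.** A reader might infer that Table 1 promises 45 scores in every row to month 6. It does not. It is an empty shell, its column number equals the number assigned, and such a heading normally means just that. For rehospitalisation and complications, 45 may even be the right denominator. This objection stands in full.

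**Silence is not an error.** The article gives no rule for missing scores and no analysis set. A condensed article commonly leaves both to the full protocol or analysis plan, so their absence is no finding. Section 2.4 also does not rule out imputation. This stands too. What remains open to comment is the method the article does name for repeated scores.

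**Unequal loss is conjecture.** Control patients have follow-up appointments, the calls are described as part of the intervention, and nothing says that scores are collected by phone. This is fair: unequal loss is plausible, not shown.

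**The figures are assumed, and the remedy was tested on favourable ground.** Loss rates, correlation and dropout slope are all assumptions, and the sign reverses with them. Recovery by the likelihood method is expected when loss depends on observed scores. If patients stop responding because of how they feel at the time, a mixed model can be biased as well. All of this stands. It limits the claim to a better choice of method and does not turn the t-test into a demonstrated error.

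**Conclusion.** The point holds as a recommendation on a stated analysis choice. Separate t-tests ignore the earlier scores of patients lost later, in a trial with scores repeated to month 6 and scheduled contact that differs by arm. If loss is both unequal and related to the patient's condition, the month-6 comparison can be biased either way, by roughly 0.06 to 0.11 SD on a true 0.5 SD under the repeated-visit assumptions.

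A reader might go further and conclude that unequal loss by itself biases the comparison, or that the plan will understate the benefit. The documents support neither: bias is zero when loss is unrelated to the score or equal in both arms under the same mechanism, and with no loss rate given neither size nor direction can be fixed.

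**What to change.** - **Section 2.4.** Analyse the Left Ventricular Dysfunction Scale with one linear mixed model for repeated measures (SPSS MIXED), and the self-care score with another at its own three intervals. Include every randomised patient with any score, in the allocated arm, with arm-by-time terms, and report the between-arm difference at each time from the model.
- **Baseline.** Include the baseline score where it is collected in both arms, and say so. Section 2.2 mentions baseline data for the intervention arm only, and Table 1 has no baseline row for the Left Ventricular Dysfunction Scale. Without this score part of the bias would remain.
- **Table 1.** Keep 45 as the number assigned and add the number analysed per arm in each row.
- **Optional.** One sensitivity analysis in which the scores of lost patients are set progressively worse, because the model still assumes that loss is explained by observed scores.

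The cost is wording in section 2.4, a small change to the table layout and a slightly more complex analysis. No further patients or follow-up visits are needed.

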## Discussion

4

Due to low life quality, high medical costs and premature death, HF has become a kind of modern epidemic, which has brought huge economic and human burden to the community.^[10,11]^ The HF patients do not have enough self-care ability, and the rehospitalization rate for these patients is high.^[12,13]^ The maintenance of self-care includes the symptoms monitoring, adaptive therapy, as well as learning to recognize the relevant symptoms. It has been stated that identifying the symptoms is a significant step in managing the self-care of HF.^[14,15]^ In order to maintain an appropriate level of self-care, patients need professional nursing care, skills and knowledge. In the past decade, various interventions have been carried out in patients with HF. The effective nursing care and educational intervention for the patients can promote the development of positive health results.^[16,17]^ With the implementation of the follow-up plan and comprehensive care, the self-care abilities of patients with HF may be improved, and the hospitalization rate of these patients may be decreased.

## Conclusion

5

We hypothesize that the nursing care conducted for the HF patients may improve the life quality and self-care.
